**Data analysis**

Data analysis will be performed according to the intention-to-treat principle. For proportion comparisons, chi-square tests will be employed. At baseline, logistic regression will be used to determine the associations between cervical cancer risk factors and HPV infection or cervical abnormalities. HPV prevalence will be calculated for participants in the intervention group. HPV clearance or persistence will be obtained by comparing those participants who have a positive HPV result at baseline and who do not require treatment for cervical lesions with their subsequent HPV testing results at 1-year post colposcopy. Clearance of mild cervical abnormalities will be obtained based on the participants with borderline cytology results at baseline and the proportion of these same participants who turn normal at subsequent screening without ever requiring treatment for cervical precancerous lesions if present. Incidence of CIN2+ will be calculated for both arms at baseline and at the second screening round. The estimated relative risks of CIN2+ will be calculated and compared at the second screening round for the control arm participants who have normal cytology results and for those in the intervention arm who have normal cytology and negative HPV results at baseline, respectively. Sensitivities, specificities, predictive values of the two screening methods for the detection of CIN2+ will be calculated based on the cervical biopsy data from participants who undergo colposcopy at baseline.

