**Study Design**

This is a prospective randomized controlled trial to study the effect of HPV-cytology co-testing as a primary screening strategy for women aged 30 years or above. Each consented participant will be randomized on a 1:1 ratio into one of two arms: Cytology arm (control) or cytology plus HPV testing arm (intervention). Participants will be followed for two rounds of screening or until the occurrence of high grade CIN, whichever takes place first. Cytology testing, HPV testing and histological studies of biopsies will be conducted by the laboratories of the University of Hong Kong. Colposcopy and biopsy, when indicated, will be performed by the colposcopists at the colposcopy clinic in Queen Mary Hospital or at the Lady Helen Woo Women’s Diagnostic and Treatment Centre. All final test reports will be reviewed and signed by the senior pathologists.

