***Control arm***

The index test for participants in the control arm will be conventional cytology testing. HPV testing will also be administered. ,HPV results will not be revealed to the participant or healthcare professionals who are involved in the direct care of the participant except in the case of reflex HPV testing for borderline cytology results. Participants will be managed based on their cytology results according to the current practice of the involved clinics and the Hong Kong College of Obstetricians and Gynaecologists Guidelines. (Fig. 1) Colposcopy will be offered in the following conditions: (1) any cytologic abnormalities greater than ASCUS, (2) ASCUS and HPV positive, or (3) two consecutive ASCUS results. In addition, a random 5% of participants with negative cytology results will be invited to attend colposcopy at baseline at the Lady Helen Woo Women’s Diagnostic and Treatment Centre.  Post colposcopy management of participants is shown in Fig. 2. Participation in the study will be terminated at a diagnosis of CIN 2 or greater.

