**Outcome Measures**

Histological CIN2, CIN3 and cervical cancer are the primary outcomes of the study. Diagnosis will be obtained through biopsies. Secondary outcomes include (1) HPV prevalence at baseline, (2) HPV clearance or persistence among participants who test positive at baseline, (3) clearance of mild cervical abnormalities among participants who test HPV negative and (4) sensitivities, specificities, predictive values of the two screening methods.

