**Sample Size Calculation**

Based on the 2004-07 registry data from the Department of Health’s Cervical Screening Programme, the local prevalence of CIN2+ was postulated to be about 1.2%. A total sample size of 12000 women will be required to detect an absolute difference of 25% in the sensitivity between the control arm and the intervention arm in the detection of CIN2+ at 80% power and alpha = 0.05 (2-sided) and to account for an estimated 10% lost to follow-up rate.

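### The clearance analysis omits the HPV-negative restriction in its own outcome definition; a lesser point is that baseline HPV prevalence uses one arm although both are HPV tested

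*Protocol*

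**What the plan says.** **Clearance.** Protocol, Outcome Measures, lists as the third secondary outcome "clearance of mild cervical abnormalities among participants who test HPV negative". Protocol, Data analysis, says: "Clearance of mild cervical abnormalities will be obtained based on the participants with borderline cytology results at baseline". It then takes the proportion of these women who become normal at later screening without needing treatment. HPV status is not mentioned.

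**Prevalence.** Outcome Measures says: "Secondary outcomes include (1) HPV prevalence at baseline". It names no arm. Data analysis says: "HPV prevalence will be calculated for participants in the intervention group". It gives no reason. The Control arm section says of that arm: "HPV testing will also be administered". It adds that, apart from reflex testing of borderline cytology, "HPV results will not be revealed to the participant or healthcare professionals who are involved in the direct care of the participant". That is a limit on disclosure, not on use in analysis.

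**Which control samples are tested, and where.** The HPV testing section sends control-arm reflex tests at baseline to the Department of Pathology laboratory, and all other HPV testing and genotyping to the Department of O&G laboratory. The title of Fig. 1 mentions only reflex HPV testing for the control arm.

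**The concern.** For clearance, the definition and the analysis name different populations. The two groups of borderline women also follow different paths. HPV-negative women are re-tested at one year (Figs. 1 and 3). HPV-positive women go to colposcopy in both arms, then to post-colposcopy smears starting at six months, and leave the study if CIN2 or worse is found (Figs. 2 and 4). A later normal result therefore comes from a different visit after a different work-up. A pooled proportion reported as the third secondary outcome would be mislabelled, and its distance from the HPV-negative rate would depend on the mix of the two groups.

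For prevalence, baseline HPV status cannot depend on the allocated arm. Leaving out the control results makes the estimate less precise than the trial can deliver. No bias follows.

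**Working it through.** The protocol states no figure for either analysis that could be reproduced. The sizes below come from its planned counts.

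**Inputs**
- Allocation: "Each consented participant will be randomized on a 1:1 ratio into one of two arms" (Study Design). "A total sample size of 12000 women will be required" (Sample Size Calculation), so 6000 per arm, as in the titles of Figs. 1 and 3.
- ASCUS at baseline, control arm: 261 (Fig. 1).
- Worse than ASCUS at baseline, control arm: 145 (Fig. 1).
- HPV-negative ASCUS, intervention arm: 130 (Fig. 3).
- HPV positive with negative cytology: 240; HPV positive with ASCUS or worse: 275 (Fig. 3).

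**Clearance population**
1. Fig. 3 gives no total for ASCUS, so the HPV-positive share needs a subtraction across arms, assuming equal baseline distributions: 261 − 130 = 131.
2. Share of the analysed group outside the defined outcome: 131/261 = 50%.
3. Consistency check: taking 131 from the 275 in Fig. 3 leaves 275 − 131 = 144 HPV-positive women with results worse than ASCUS. Fig. 1 expects 145 women with such results, so the subtraction is compatible with both figures.
4. Over both arms, the analysed group is 2 × 261 = 522 and the defined group 2 × 130 = 260.
5. Illustration only, because the protocol gives no clearance rates. Let c₋ and c₊ be the rates in HPV-negative and HPV-positive women. The pooled rate is (130/261)·c₋ + (131/261)·c₊, which lies below c₋ by 0.502 × (c₋ − c₊). Assume c₋ between 70% and 90% and c₊ between 30% and 60%:
   - lowest pooled rate (70%, 30%): 49.9%;
   - highest pooled rate (90%, 60%): 74.9%;
   - smallest gap (70%, 60%): 0.502 × 10 = 5 points;
   - largest gap (90%, 30%): 0.502 × 60 = 30 points.

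**Prevalence precision**
1. Planned prevalence: (240 + 275)/6000 = 515/6000 = 8.58%.
2. 95% half-width: 1.96 × √(p(1 − p)/n).
   - One arm, n = 6000: 1.96 × √(0.0858 × 0.9142/6000) = 0.71 points.
   - Both arms, n = 12000: 0.50 points.
3. The one-arm interval is √2 = 1.41 times as wide, a difference of 0.21 points in half-width.
4. The Fig. 1 cells sum to 5544 + 261 + 145 = 5950, not 6000. With 5950 per arm the half-widths are 0.71 and 0.50 (unrounded 0.714 and 0.505), so nothing changes.

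**A trap in pooling the arms**

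Suppose control women with borderline cytology have only the Pathology reflex result, and pooling used only O&G results. The 261 ASCUS women would drop out of the control arm, about 131 of them HPV positive.
- Control prevalence: (515 − 131)/(6000 − 261) = 384/5739 = 6.7%.
- Pooled prevalence: (515 + 384)/(6000 + 5739) = 899/11739 = 7.7%, against 8.6%.

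That downward shift of about 0.9 points is larger than the 0.21 points gained in half-width.

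**The case against.** **On clearance.** Outcome Measures sets the population and Data analysis may only describe the calculation, so the HPV-negative condition could be taken as carried over. The pathways give this some support, since HPV-negative ASCUS women are the ones sent directly to repeat screening. But Data analysis names its own population, and HPV-positive women also have later smears after colposcopy, so the wider reading is the literal one and can be carried out. The objection shows that the repair is short, not that it is unnecessary. It is also right that 131 is a cross-arm subtraction and that the size of any distortion is unknown without clearance rates.

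**On prevalence.** Randomisation keeps the intervention-arm estimate unbiased, the outcome is descriptive with no precision target, and using a single laboratory is a plausible, though unstated, reason for the restriction. All of this stands. The Control arm section also gives no time point for the HPV test, and the Fig. 1 title points to reflex testing only. If only reflex testing were done, control data could not give prevalence. The Control arm text says otherwise in plain terms, but the places need aligning.

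**Stronger readings that the protocol does not support.** A reader might infer that the one-arm restriction weakens the hypothesis on HPV genotypes. That hypothesis concerns CIN2+ or HGSIL risk by genotype among infected women and does not rest on the prevalence estimate. A reader might also infer that the risk-factor regression is limited to one arm, but Data analysis sets no such limit. Nor are treated women counted as cleared: Data analysis already excludes them from the cleared group.

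**Conclusion.** The clearance point holds and is the main one: as written, the analysis does not estimate the third secondary outcome. About half of the analysed women would lie outside the definition. This rests on the planned counts in Figs. 1 and 3 and on arms balanced by randomisation. The 5 to 30 point gap rests wholly on assumed clearance rates and shows only that the mismatch could matter.

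The prevalence point holds as a minor one. The cost is a half-width of 0.71 instead of 0.50 points around 8.6%, assuming that every control participant has a valid baseline HPV result. It would be wrong to call the one-arm estimate biased. Neither point touches the primary outcome.

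**What to change.** 1. **Clearance.** In Data analysis, restrict the calculation to women with borderline cytology who are HPV negative at baseline, in both arms, and report HPV-positive women separately. Control women with borderline cytology have a reflex HPV result, so the restriction can be applied in both arms whichever other control samples are tested. The cost is a smaller denominator: at an assumed clearance of 70%, the 95% half-width is 5.6 points with 260 women, against 3.9 with 522.
2. **Prevalence.** Calculate it in all participants with a valid baseline HPV result, overall and by arm. Keep control women with borderline cytology by using their reflex result where no O&G result exists, and add a check by laboratory.
3. **Alignment.** Make the Control arm section, the HPV testing section and the Fig. 1 title agree on which control samples are HPV tested, when, and in which laboratory.

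These are wording changes. Masked control results would be used only in analysis, so disclosure to participants and care staff stays as planned.

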***Intervention arm***

The index test in the intervention arm will be concomitant cytology testing and HPV testing. Participants will be managed based on both their cytology and HPV results in accordance with the routine practice of the involved clinics, the Hong Kong College of Obstetricians and Gynaecologists Guidelines and expert opinion on the management following a positive HPV testing result. (Fig. 3) Participants who are HPV negative with borderline cytology at baseline will be re-tested in 12 months by cytology and HPV testings. For this study, HPV positivity is defined as the presence of one or more high-risk HPV subtypes. Colposcopy will be offered in the following conditions: (1) any cytologic abnormalities greater than ASCUS regardless of the HPV result or (2) two consecutive ASCUS results regardless of the HPV results or (3) HPV positivity. Post colposcopy management of participants is shown in Fig. 4. Participation in the study will be terminated at a diagnosis of CIN 2 or greater.

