**Hypotheses**

- There is a significant difference in the number of CIN2+ cases detected between the cytology testing group and the cytology-HPV co-testing group at baseline.
- Significantly more CIN2+ cases will be detected at the second round of screening among participants with normal cytology result in the control arm than those with normal cytology and negative HPV results in the intervention arm.
- Cases infected by certain HPV genotypes are at higher risk of developing CIN2+ or HGSIL than those infected by other HPV genotypes.

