|  |  |  |  |  |  | **reflex HPV testing** |  |  |  |  |  |  |  |  |  |
|  |  |  |  |  |  |  |  |  |  |  |  |  |  |  |  |
|  |  |  |  |  | **H-** |  | **H+** |  |  |  |  |  |  |  |  |
|  |  |  |  |  |  |  |  |  |  |  |  |  |  |  |  |
|  |  |  |  |  |  |  | **Bx** |  |  |  |  |  |  |  |  |
| **1y** |  |  |  |  | **Pap** |  |  |  |  |  |  |  |  |  |  |
|  |  |  |  |  |  |  |  |  |  |  |  |  |  |  |  |
|  |  |  |  | **C-** |  | **≧A** |  |  |  |  |  |  |  |  |  |
|  |  |  |  |  |  |  |  |  |  |  |  |  |  |  |  |
|  |  |  |  |  |  | **Bx** |  |  |  |  |  |  |  |  |  |
| **3y** | **Pap** |  |  |  |  |  |  |  |  |  |  |  |  |  |  |
|  |  |  |  |  |  |  |  |  |  |  |  |  |  |  |  |
| **4y** |  |  |  | **Pap** |  |  |  |  |  |  |  |  |  |  |  |
|  |  |  |  |  |  |  |  |  |  |  |  |  |  |  |  |

Fig. 2 Control arm (post colposcopy – biopsy)

| **0** |  |  |  |  |  |  |  |  |  |  | **Bx** |  | Rules:   1. After Bx, Pap x 3 q6m. If 3 consecutive C-  routine screening 2. After Bx, if 2 consecutive A/LSIL  repeat Bx 3. Any > CIN1  out study   *CIN 1 in > 2 quad or persist for > 2yrs  Tx  Bx = colposcopy +/- biopsy Tx = treatment  C = cytology  A = Ascus  PapR = routine screening |
| --- | --- | --- | --- | --- | --- | --- | --- | --- | --- | --- | --- | --- | --- |
|  |  |  |  |  |  |  |  | **Normal / HPV / CIN 1*** | |  |  | **CIN 2-3 / invasive** | |
|  |  |  |  |  |  |  |  |  |  |  |  | **Tx, Out** |  |
| **6m** | **post** |  |  |  |  |  | **Pap** |  |  |  |  |  |  |
|  |  |  |  |  |  |  |  |  |  |  |  |  |  |
|  |  |  |  |  |  |  |  |  |  |  |  |  |  |
|  |  |  |  |  | **C- / A / LSIL** |  |  |  | **HSIL** |  |  |  |  |
|  |  |  |  |  |  |  |  |  |  |  |  |  |  |
|  |  |  |  |  |  |  |  |  | **Bx** |  |  |  |  |
| **1y** | **post** |  |  |  | **Pap** |  |  |  |  |  |  |  |  |
|  |  |  |  |  |  |  |  |  |  |  |  |  |  |
|  |  |  |  |  |  |  |  |  |  |  |  |  |  |
|  |  |  | **C-** |  | **≧A** |  |  |  |  |  |  |  |  |
|  |  |  |  |  |  |  |  |  |  |  |  |  |  |
|  |  |  |  |  | **Bx** |  |  |  |  |  |  |  |  |
|  |  |  |  |  |  |  |  |  |  |  |  |  |  |
| **1.5 y** | **post** |  | **Pap** |  |  |  |  |  |  |  |  |  |  |
|  |  |  |  |  |  |  |  |  |  |  |  |  |  |
|  |  |  | **C-** | **≧A** |  |  |  |  |  |  |  |  |  |
|  |  |  |  |  |  |  |  |  |  |  |  |  |  |
| **4.5 y** | **post** |  | **PapR** |  |  |  |  |  |  |  |  |  |  |
|  |  |  |  |  |  |  |  |  |  |  |  |  |  |

Fig. 3 Intervention arm (conventional cytology testing & HPV testing) n = 6000

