|  | **1** |  |  |  | **2** |  |  |  |  | **3** |  |  |  | **4** |  |  | **5** |
| --- | --- | --- | --- | --- | --- | --- | --- | --- | --- | --- | --- | --- | --- | --- | --- | --- | --- |
| **0** | **H-,C-** |  |  |  | **H-,A**  **n = 130** |  |  |  |  | **H-,>A** |  |  |  | **H+,C-**  **n = 240** |  |  | **H+,≧A**  **n = 275** |
|  |  |  |  |  |  |  |  |  |  |  |  |  |  | **Bx** |  |  |  |
| **1y** |  |  |  |  | **PapH** |  |  |  |  |  |  |  |  |  |  |  |  |
|  |  |  |  |  |  |  |  |  |  |  |  |  |  |  |  |  |  |
|  |  |  | **H-,C-** | **H-,≧A** | **H+,≧A** | **H+,C-** |  |  |  |  |  |  |  |  |  |  |  |
|  |  |  |  |  | **Bx** |  |  |  |  |  |  |  |  |  |  |  |  |
| **2y** |  |  |  |  |  |  |  |  |  |  |  |  |  |  |  |  |  |
|  |  |  |  |  |  |  |  |  |  |  |  |  |  |  |  |  |  |
|  |  |  |  |  |  |  |  |  |  |  |  |  |  |  |  |  |  |
| **3y** | **Pap** |  |  |  |  |  |  |  |  |  |  |  |  |  |  |  |  |
| **4y** |  |  | **Pap** |  |  |  |  |  |  |  |  |  |  |  |  |  |  |

Rules: (1) baseline: any >A Bx

(2) throughout, any H+  Bx

(3) 2 consecutive A, H+/-  Bx

H = HPV, C = cytology, A = Ascus, PapH = pap & HPV test, Bx = colposcopy +/- biopsy

Fig. 4 Intervention arm (post colposcopy – biopsy)

| **0** |  |  |  |  |  |  |  |  |  |  |  | **Bx** |  | Rules:   1. If 2 consecutive H-&C-  routine screening 2. Any H+ or C+ at / after 1st y post Bx  repeat Bx   *CIN 1 in > 2 quad or persist for > 2yrs  Tx  Bx = colposcopy +/- biopsy  Tx = treatment  PapH = pap & HPV  H = HPV  C = Cytology  PapR = routine screening |
| --- | --- | --- | --- | --- | --- | --- | --- | --- | --- | --- | --- | --- | --- | --- |
|  |  |  |  |  |  |  |  |  |  | **≦CIN 1*** |  |  | **>CIN 1** |  |
|  |  |  |  |  |  |  |  |  |  |  |  |  | **Tx, Out** |  |
| **6m** | **post** |  |  |  |  |  |  |  | **Pap only** |  |  |  |  |  |
|  |  |  |  |  |  |  |  |  |  |  |  |  |  |  |
|  |  |  |  |  |  |  |  |  |  |  |  |  |  |  |
|  |  |  |  |  |  |  |  |  | **C- /A / LSIL** | **HSIL** |  |  |  |  |
|  |  |  |  |  |  |  |  |  |  |  |  |  |  |  |
|  |  |  |  |  |  |  |  |  |  | **Bx / Tx, Out** |  |  |  |  |
| **1y** | **post** |  |  |  |  |  |  |  | **PapH** |  |  |  |  |  |
|  |  |  |  |  |  |  |  |  |  |  |  |  |  |  |
|  |  |  |  |  |  |  |  |  |  |  |  |  |  |  |
|  |  |  |  |  |  | **H-,C-** | **H+,C-** |  | **A / LSIL / HSIL (H+/-)** |  |  |  |  |  |
|  |  |  |  |  |  |  |  |  |  |  |  |  |  |  |
|  |  |  |  |  |  |  |  |  | **Bx** |  |  |  |  |  |

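### CIN2+ found between the two screening rounds is a primary-outcome event with no stated place in the by-arm incidence, and the gap probably falls somewhat more on the co-testing arm

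*Protocol*

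**What the plan says.** Outcome Measures sets the endpoint without a time window: "Histological CIN2, CIN3 and cervical cancer are the primary outcomes of the study". Study Design sets follow-up: "Participants will be followed for two rounds of screening or until the occurrence of high grade CIN, whichever takes place first". The Intervention arm section adds "Participation in the study will be terminated at a diagnosis of CIN 2 or greater", and the Control arm section has the same rule.

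Data analysis then states: "Incidence of CIN2+ will be calculated for both arms at baseline and at the second screening round". The Hypotheses use the same two points. The first reads "There is a significant difference in the number of CIN2+ cases detected between the cytology testing group and the cytology-HPV co-testing group at baseline". The second, with the matching relative risk in Data analysis, concerns the second round and is restricted to cytology-negative controls against "those in the intervention arm who have normal cytology and negative HPV results at baseline".

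The figures schedule detection in between:

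- Figs. 1 and 3: a 1-year retest of women with ASCUS and a negative HPV test, in both arms.
- Fig. 2, rule 1 (control, after colposcopy): "After Bx, Pap x 3 q6m", that is, smears at 6, 12 and 18 months.
- Fig. 4 (intervention, after colposcopy): a smear at 6 months, then smear plus HPV test at 1 and 2 years. Under rule 2 the trigger for repeat colposcopy is "Any H+ or C+ at / after 1st y post Bx".

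Routine screening follows at about 3 to 5 years, depending on the path.

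**The concern.** A woman whose CIN2+ is found at one of these intermediate visits has the primary outcome, leaves the study and cannot contribute at the second round. If baseline means time 0, she is in neither incidence figure. The Protocol never says so outright, but its usage points that way. The Intervention arm section sets baseline apart from the 12-month retest, and Data analysis sets it apart from the HPV test one year after colposcopy. The section also declares an intention-to-treat analysis, which sits badly with randomised women who have the primary outcome and no place in the count.

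Two things are at stake. First, the number of such women differs by design between the arms, so an unrestricted second-round incidence by arm may be distorted. Second, two separate snapshots cannot show whether co-testing finds the same lesions sooner or finds additional ones. Only a total over both rounds can.

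**Working it through.** **1. Inputs.** Planned baseline counts, 6,000 per arm:

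- Fig. 1 (control): cytology-negative 5,544; ASCUS 261; above ASCUS 145; random colposcopy sample 277. The sample reproduces: 0.05 × 5,544 = 277.2. The three cytology groups sum to 5,950; nothing below depends on the remaining 50.
- Fig. 3 (intervention): HPV-negative ASCUS 130; HPV-positive, cytology-negative 240; HPV-positive with ASCUS or worse 275.
- Sample Size Calculation: CIN2+ prevalence 1.2%; planned difference in sensitivity 25 points.

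**2. Women sent to colposcopy by their baseline tests**, assuming the same cytology and HPV distribution in both arms:

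- ASCUS, HPV-positive: 261 − 130 = 131
- Above ASCUS, HPV-positive: 275 − 131 = 144
- Above ASCUS, HPV-negative: 145 − 144 = 1
- Intervention: 240 + 275 + 1 = 516
- Control: 145 + 131 = 276
- Intervention share: 516 / (516 + 276) = 65%

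Adding the 277 random controls gives 276 + 277 = 553, and the intervention share by head count falls to 516 / (516 + 553) = 48%. Those 277 are cytology-negative, and only about 0.05 × 240 = 12 would be HPV-positive. Counting HPV-positive women sent to colposcopy: 515 in intervention against 131 + 144 + 12 = 287 in control, or 64% in intervention. All these counts are before removal of CIN2+ found at baseline.

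**3. One-year retest.** Intervention 130; control 261 − 131 = 130. There is no numerical imbalance.

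**4. Share of interim CIN2+ in the intervention arm.** The Protocol gives no interim yield, so risks are assumed relative to the other referred women. Let *k* be the relative risk in HPV-positive, cytology-negative women (0.1 to 1), *d* the detection advantage of the intervention schedule (1 to 1.5), and *m* the relative risk in the 277 − 12 = 265 HPV-negative random controls (0 to 0.1). Retested women are given relative risk 0.25.

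- I = d × (276 + 240k + 130 × 0.25)
- C = 276 + 12k + 265m + 130 × 0.25
- Share = I / (I + C)

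Results:

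- Lowest (k = 0.1, d = 1, m = 0.1): 332.5 / (332.5 + 336.2) = 49.7%
- Middle (k = 0.5, d = 1, m = 0.05): 428.5 / (428.5 + 327.75) = 56.7%
- Highest (k = 1, d = 1.5, m = 0): 822.75 / (822.75 + 320.5) = 72.0%

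Of 24 combinations tried, only the lowest is below 50%.

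**5. Illustrative case numbers**, for an assumed interim risk *r* of 1% to 5% and *k* of 0.25 to 1, leaving out the retested women and the HPV-negative random controls:

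- r = 1%, k = 0.25: intervention 0.01 × (276 + 60) = 3.4; control 0.01 × (276 + 3) = 2.8; gap 0.6
- r = 5%, k = 1: intervention 0.05 × 516 = 25.8; control 0.05 × 288 = 14.4; gap 11.4

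For scale, expected prevalent CIN2+ is 0.012 × 6,000 = 72 per arm, and the planned difference is 0.25 × 72 = 18 detected cases. The upper end is generous. If intervention sensitivity is 75% to 90% (assumed), 54 to 65 cases are found at baseline and only 7 to 18 prevalent cases remain in the whole arm, so 25.8 interim cases would need at least about 8 incident ones.

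**6. Which comparisons are touched.** Cytology-negative controls and double-negative intervention women have no scheduled visit before the 3-year smear, apart from the 277 random controls. The restricted relative risk therefore loses little. The unrestricted incidence by arm is the one affected: about 240 − 12 = 228 control women who are HPV-positive and cytology-negative wait for the 3-year smear, where CIN2+ is counted if the smear finds it. CIN2+ found during surveillance in the 240 intervention women after a baseline colposcopy showing no CIN2+ has no assigned count.

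**The case against.** The strongest reply is that the Protocol is silent rather than wrong. It nowhere drops interim cases, it defines neither round formally, and surveillance could be read as completing the work-up of the first-round result. Assigning events to windows is also often left to a statistical analysis plan. Part of this stands: the cases are unassigned, not expressly excluded. But the first-round-episode reading is nowhere stated and runs against the Protocol's own use of baseline. The two counting points are fixed in the Protocol itself. Left open, the cases could join baseline, join the second round or disappear after results are known.

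Several stronger readings are tempting, and the documents do not support them:

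- **That the lost cases fall mostly in the intervention arm.** This rests on assumed yields. A modest majority is likely, and near-equality is possible.
- **That every later intervention CIN2+ is uncounted.** After two consecutive double-negative results women return to routine screening (Fig. 4), where CIN2+ can still count.
- **That the arms lose and keep the same kind of women.** Intervention women under surveillance have had a biopsy in each quadrant and curettage showing no CIN2+. Nearly all their control counterparts are unbiopsied and still carry prevalent disease. A lower later yield after earlier detection is partly the effect under study.
- **That both hypotheses fail.** Hypothesis 1 as a time-0 comparison and the restricted relative risk are largely intact. The HPV-positive women are outside that relative risk by its definition, not through the counting gap.

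Nothing is lost irrecoverably either, since follow-up to high-grade CIN means that interim cases are ascertained.

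**Conclusion.** The point holds in a limited form. As written, the by-arm incidence has no place for CIN2+ found between the rounds, although it is the primary outcome. The imbalance follows from design: about 516 against 276 test-triggered baseline colposcopies, and HPV-based surveillance of the 240 HPV-positive, cytology-negative women in one arm only. The intervention share of interim cases is about 50% to 72% under the risks tried, and the 1-year retest adds nothing to it numerically. The illustrative gap runs from under 1 case to about 11, against a planned difference of about 18.

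The likely direction is a second-round incidence by arm that looks too favourable to co-testing. Its size cannot be established from the Protocol. These figures assume equal test distributions in the arms and invented interim risks. What does not depend on them is that events of the primary outcome lack a counting rule, and that no cumulative comparison is described.

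**What to change.** In Data analysis:

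1. Define baseline, interim and second round, and assign every histological CIN2+ to exactly one: the baseline tests and their colposcopy; the 12-month retest and post-colposcopy surveillance; or the second-round screen and its work-up.
2. Make the unrestricted post-baseline comparison interim plus second round, by randomised arm.
3. Add cumulative CIN2+ and CIN3+ from randomisation to the end of the second round, with all randomised women as denominator and each woman counted once.
4. Keep the restricted relative risk as a separate, labelled analysis.

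The cost is wording and one more table. The data are already collected and no patient's management changes. The price is that the second-round contrast may look less favourable to co-testing.
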